### ***1.2. Medication Management***

Effective medication management is essential for improving outcomes following PCI, and in the intervention group, nurses provided comprehensive medication education to ensure that patients understood the importance of their prescribed treatments. This education covered the correct timing, dosage, and potential side effects of medications, along with guidance on how to manage and adjust medications based on specific health indicators such as blood pressure and blood glucose levels. Nurses held one-on-one sessions twice a week to reinforce medication adherence, clarify any misconceptions, and ensure patients fully understood their treatment regimens.

In addition to medication education, patients were informed about behaviors that could help maintain their health and support recovery. Videos featuring healthcare practitioners were used to explain the role of medications like statins, aspirin, and Tegretol in stabilizing coronary arteries, alongside information about other common medications such as angiotensin-converting enzyme inhibitors and receptor blockers. Educational content also included guidance on adopting a healthy lifestyle, including the importance of diet, exercise, smoking cessation, and returning to normal activities and work. This information was provided through an interactive mind map accessible via QR codes, aimed at helping patients navigate their recovery process and alleviate anxiety related to their condition.

The comprehensive approach to medication management was part of a broader

strategy to empower patients with the knowledge and tools necessary to take control of their health. By combining education on medication with lifestyle advice, this intervention aimed to improve both adherence to prescribed treatments and overall well-being during recovery.

### ***1.3. Nutritional Guidance***

Nutritional support plays a vital role in preventing further cardiovascular events and promoting long-term health. The intervention group received tailored nutritional guidance focused on heart-healthy diets. Nurses provided educational sessions on the importance of a balanced diet, including the reduction of saturated fats, increased intake of fruits and vegetables, and moderation of sodium and sugar. Patients were educated on how dietary modifications could support weight management, blood lipid control, and overall cardiovascular health. In addition, dietary suggestions were personalized according to each patient's health condition and preferences, ensuring feasibility and sustainability.

### ***1.4. Psychological Support***

Psychological well-being is a crucial factor in the recovery of cardiovascular patients, especially following a major procedure such as PCI. To address the psychological needs of patients, the intervention group received regular psychological support. Nurses conducted weekly sessions focused on stress management, coping strategies, and emotional well-being. The program included guided relaxation techniques, mindfulness exercises, and educational resources aimed at reducing anxiety, depression, and fear related to recovery. The psychological support sessions were designed to enhance patients' mental resilience, improve their emotional responses to recovery, and encourage a more positive outlook toward rehabilitation.

### ***1.5. Sleep Management***

Poor sleep quality is a common concern for cardiovascular patients, and sleep disturbances can negatively affect recovery outcomes. As part of the intervention, patients received sleep management strategies. Nurses provided education on good sleep hygiene practices, such as establishing a regular sleep schedule, avoiding stimulants before bed, and creating a conducive sleep environment. For patients

reporting persistent sleep difficulties, personalized strategies were developed to help improve sleep quality and promote overall recovery.

### ***1.6. Health Education***

Health education was a central component of the rehabilitation program, aimed at empowering patients to actively participate in their recovery. The intervention group received educational materials covering key topics such as disease understanding, PCI recovery, lifestyle modifications, and self-management techniques. Educational content was delivered through videos, images, and written explanations integrated into the digital platform, allowing patients to access information at their convenience. The program used simple, clear language and was accompanied by audio and subtitles in standard Mandarin to ensure accessibility, especially for those with language or literacy barriers.

### ***1.7. Smoking Cessation Assistance***

Smoking cessation is essential for improving cardiovascular health and preventing future complications. In the intervention group, nurses provided ongoing smoking cessation support through counseling and educational sessions. Patients were educated on the harmful effects of smoking on heart health and were offered strategies to quit smoking, including behavioral therapy, nicotine replacement options, and motivational support. Progress was monitored regularly, and patients received personalized feedback and encouragement to help them stay on track with their cessation goals.

## ***2. Post-Discharge Rehabilitation***

Upon discharge, patients continued to receive individualized follow-up education through WeChat software during the first, second, and third months post-surgery. In addition, patients were scheduled for outpatient follow-up visits during the third months post-surgery. These follow-up sessions allowed the multidisciplinary intervention team to monitor the patients' progress in terms of physical activity, dietary habits, sleep quality, psychological status, and smoking cessation efforts.

Personalized rehabilitation plans were adjusted according to each patient's ongoing needs and progress.

At discharge, patients' families were trained on how to assist in symptom recognition and management, reinforcing the importance of family support in the rehabilitation process. All rehabilitation materials were provided as QR codes to facilitate patient self-learning and easy access to ongoing educational content.

### ***Development and Quality Control***

The content of the cardiac rehabilitation program package was entirely developed by a multidisciplinary team comprising cardiovascular nurses, clinicians, and rehabilitation physicians. The team systematically reviewed the best available evidence on exercise rehabilitation for coronary artery disease patients and incorporated it into the program. To ensure accessibility and effectiveness, the program utilized simple language, videos, audio, and subtitles in standard Mandarin. Regular quality control procedures and feedback mechanisms were implemented to assess and optimize the program's efficacy throughout the study period.

### **Control group**

The control group received only routine nursing care and health education, which was implemented through verbal education combined with the "317 Nursing Education Platform"; routine health education included admission education, preoperative and postoperative education, discharge guidance, and health education at any time during the treatment process. In the control group, no specific individual exercise instructions were provided, especially regarding preoperative and postoperative activities.

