resources or those unable to attend regular outpatient treatments due to work or lifestyle factors. Moreover, the digital rehabilitation package enables real-time monitoring of the patient's rehabilitation progress, facilitating timely adjustments to treatment plans and ensuring optimal rehabilitation outcomes. Through this digital intervention model, we can significantly improve patient adherence to rehabilitation and treatment outcomes, providing a feasible practical solution for the future of digital health management.

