#### ***1.1 Exercise Training***

Exercise rehabilitation is a critical component of recovery following PCI, and the intervention group received personalized exercise plans designed to enhance cardiovascular health and physical capacity. During hospitalization, nurses delivered the exercise programs using multimedia-equipped bedside tablet computers, incorporating a variety of interactive materials such as instructional videos, images, and written explanations to ensure patients performed exercises correctly. Nurses provided one-on-one guidance during twice-weekly sessions, with a particular focus on progressive muscle strengthening, aerobic training, and flexibility. To accommodate varying physical capabilities, the exercise program was developed using Flash frame-by-frame animation technology, which allowed for clear visualization of movements, making it easier for patients to follow and execute exercises accurately.

Unlike previous studies, this research tailored the exercise interventions specifically for UA patients undergoing PCI, ensuring the exercises were suitable for individual fitness levels. The program incorporated "Baduanjin" exercises, optimizing movements based on patient age and physical condition, and ensuring accessibility for a diverse range of patients. Each participant received a written rehabilitation

prescription, which included a warm-up phase, aerobic training, strength training, balance exercises, and a cool-down period. The intensity of exercises was adjusted based on the patient's Borg score following a 6-minute walking test, combined with noninvasive cardiac output monitoring to ensure safety and effectiveness.

This individualized rehabilitation program was integrated into the bedside tablet computers, allowing patients to learn and replicate exercises through interactive content. Nurses reinforced the proper execution of the program, ensuring that the rehabilitation process was followed correctly and effectively. The overall goal was to provide a comprehensive, personalized exercise regimen that supported recovery, enhanced physical capacity, and catered to the diverse needs of the patient population.

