## Discussion

Findings indicated that a multidimensional digital CR intervention improved functional status (FP, 6MWT, gait speed, and 30-s CST) and metabolic markers (TC, TG, and LDL-C) in patients with UA undergoing PCI within a relatively short period compared to standard management. These results emphasize the program's potential to enhance physical recovery and cardiovascular health. Significant time effects were also observed for grip strength, WC, BMI, and overall quality of life (physical and mental components), reinforcing the efficacy of digital interventions. This novel rehabilitation model provides CVD education, clarifies essential diagnostic procedures, provides exercise rehabilitation guidance, and supports home-based rehabilitation. Promoting physical activity, encouraging lifestyle modifications, and facilitating behavioral changes during recovery contribute to improved quality of life in patients with UA undergoing PCI.

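### The trial can estimate the effect of a whole nurse-led package, not of digital delivery, so the two statements that credit mHealth or digital interventions go beyond the design

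*Combined protocol and SAP*

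**What the plan says.** **Intervention arm.** The in-hospital sections describe a written, individual exercise prescription and regular nurse contact. On exercise: "Nurses provided one-on-one guidance during twice-weekly sessions". Medication Management adds one-on-one nurse sessions, also twice a week. Psychological Support adds a weekly element: "Nurses conducted weekly sessions focused on stress management, coping strategies, and emotional well-being". Further sections cover nutrition, sleep, health education and smoking cessation. Study Design and Post-Discharge Rehabilitation add training of family members. Delivery uses bedside tablets, QR codes and WeChat.

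**Control arm.** The Control group section says: "The control group received only routine nursing care and health education". Education was verbal, combined with the "317 Nursing Education Platform". On exercise, "no specific individual exercise instructions were provided, especially regarding preoperative and postoperative activities".

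**What is claimed.** The overall aim in the Introduction, the Study Purpose, the opening of Study Design and the first Discussion sentence ("Findings indicated that a multidimensional digital CR intervention improved functional status", compared with standard management) all concern the programme as a whole or do not mention the medium. Two places go further. Objective (2) in the Introduction asks what mHealth does for adherence, self-management and psychological well-being. Later in its paragraph, the Discussion takes significant time effects on grip strength, waist circumference, BMI and quality of life as strengthening the case for digital interventions.

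**The concern.** The arms differ in more than the medium. One arm was given an individual exercise programme, scheduled nurse contact and family training. The other had no individual exercise instruction, and no such sessions are described for it. A difference in the 6-minute walk, frailty or SF-12 could come from any of these elements or from their combination.

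What is at stake is how the result is used. If the benefit is credited to digital delivery, a hospital could adopt the videos and QR codes without the nurse sessions or the prescription and expect the same gain. This trial gives no evidence for that.

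**Working it through.** The documents state no effect size, power or sample-size figure on this point, so there is no plan figure to reproduce. The check compares the arms and adds one count.

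**1. The arms side by side**

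| Element | Intervention | Control | Source |
|---|---|---|---|
| Individual exercise prescription | Yes | No individual exercise instruction | 1.1 Exercise Training; Control group |
| One-on-one exercise sessions | 2 per week in hospital | None described | 1.1; Control group |
| One-on-one medication sessions | 2 per week | None described | 1.2; Control group |
| Psychological sessions | 1 per week (not stated to be one-on-one) | None described | 1.4; Control group |
| Family training | Yes | None described | Study Design; Post-Discharge Rehabilitation |
| Health education | Yes, on the digital platform | Yes, verbal plus a named platform | 1.6; Control group |
| Monthly WeChat sessions | Yes | Sections conflict (step 4) | Study Design; Post-Discharge Rehabilitation; Control group |

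**2. What two arms identify.** Write C for exercise and other rehabilitation content, N for nurse contact, F for family involvement and D for digital medium. The trial yields one contrast:

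mean(intervention) − mean(control) = joint effect of the differences in C, N, F and D.

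That is one equation for at least four component effects, before any interactions. To isolate D, the intervention arm would have to be compared with an arm that had the same C, N and F but no digital medium. No such arm exists. Propensity matching (68 + 68 = 136 patients) works on baseline covariates. Even if it balanced them perfectly, it could not separate components that were assigned together, and neither could a larger sample.

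**3. Size of the non-digital difference**

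- Separate visits: 2 (exercise) + 2 (medication) + 1 (psychological) = 5 scheduled nurse sessions per week.
- Exercise and medication sharing a visit: 2 + 1 = 3 per week.

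The documents do not say which applies. They also give no length of stay, so total contact is unknown. With an assumed stay of 1 to 2 weeks it runs from 3 × 1 = 3 to 5 × 2 = 10 sessions.

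**4. Follow-up contact.** Study Design says that both groups were followed for three months and describes that follow-up as including monthly individualized WeChat sessions. Post-Discharge Rehabilitation sets out the WeChat education as part of the intervention. The Control group section does not mention it.

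- If Study Design is right, both arms had a digital channel after discharge, and the contrast says even less about D.
- If only the intervention arm had it, D still changes together with C, N and F.

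Neither reading isolates the medium.

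**5. The time effects.** A time effect describes change from baseline to three months. It is not, as such, a difference between arms. The Discussion sentence does not state between-group differences for the outcomes it lists, and the Statistical Method section describes two-group comparisons only, with no model containing a time term. That sentence therefore supports neither the medium nor, as written, the package.

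**The case against.** The strongest reply is that the declared question is a programme against usual care. That is a legitimate pragmatic comparison, and a comparator with matched content would be a different trial. This stands. The overall aim in the Introduction, the Study Purpose, the opening of Study Design and the first Discussion sentence are all statements that this comparator can address, leaving aside the separate matter of non-random allocation. A reader might infer that the objectives and conclusions as a whole credit digital delivery; the documents do not support that.

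It can also be said that the Study Rationale sentence "Through this digital intervention model, we can significantly improve patient adherence to rehabilitation and treatment outcomes" refers to the package and states an expectation. That is fair. Neither that sentence nor objective (3), on promoting digital health, has to be deleted.

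The nurse exercise sessions used bedside tablets, so contact and medium are partly intertwined. That is true, and it is a further reason why they cannot be separated.

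Some stronger readings of the comparator should also be resisted:

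- **Controls had no one-on-one contact.** The Control group section rules out only individual exercise instruction. It is silent on other individual contact and allows education at any time during treatment.
- **All seven dimensions were absent in controls.** Health education is one of the seven, and controls received it.
- **At least five nurse sessions per week.** This assumes separate visits; three is also compatible with the text.
- **A gain was to be expected without any digital component.** The Introduction calls traditional rehabilitation effective for cardiovascular mortality and quality of life. It does not say so for the 6-minute walk or frailty.
- **The control platform was digital.** This is plausible but not stated, and the point does not need it.

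**Conclusion.** The point holds in a limited form. The trial can estimate the effect of a nurse-led, in-person and digital package against routine care and education without individual exercise instruction. It cannot estimate an effect of digital delivery. Objective (2) in the Introduction and the Discussion sentence on time effects go beyond that; the package-level statements do not.

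No numerical share can be assigned to the medium, because that share is not identified. The visible non-digital difference is the individual exercise prescription, family training and 3 to 5 scheduled inpatient nurse sessions per week against none described. This rests on reading the Control group section's silence as no scheduled sessions. If controls did have some, the contact difference shrinks, but there is still no arm with matched content and contact and no digital medium. The conclusion also holds under either reading of the WeChat follow-up.

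**What to change.** 1. Reword objective (2) in the Introduction and the Discussion sentence on time effects so that both refer to the whole nurse-led package, in-person and digital, against routine care and education without individual exercise instruction.
2. In the Discussion sentence, report between-group differences for the outcomes listed, or say that only change over time was seen.
3. State that digital and conventional rehabilitation were not compared and that no effect can be credited to the medium alone.
4. Reconcile Study Design, Post-Discharge Rehabilitation and Control group on the monthly WeChat sessions, and state which follow-up contacts controls received.

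The cost is wording, plus a check of what follow-up controls were given. No new patients or data collection are needed. The downside for the sponsor is a conclusion less favourable to digital delivery.

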### **Randomization**

Owing to the nature of the intervention, the participants were not randomly assigned. To minimize potential confounding factors, the multidimensional digital cardiac rehabilitation intervention group and the usual care group were matched on the basis of propensity scores calculated using logistic multiple regression analysis. The matching process involved considering covariates such as age, sex, education level, marital status, exercise habits, monthly salary, current address, living arrangement

(solitary or not), history of CHD, history of PCI, length of hospitalization, medical insurance status and polypharmacy data obtained from presurveys. Propensity score analysis was conducted using a 1-to-1 ratio matching approach with the nearest neighbour method to ensure balanced characteristics between the intervention and control groups. A standard calliper width of 0.2 was used for the propensity score. After matching, a total of 136 patients were included, with 68 patients in the multidimensional digital cardiac rehabilitation group and 68 patients in the usual care group.

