159 research team will ensure that patients have signed the informed consent form before  
160 entering the study and will provide ongoing support and guidance throughout the  
161 study.

162 After the recruitment and pre-screening processes, patients were divided into two  
163 groups based on their admission dates: the control group (April to May 2022) and the  
164 intervention group (May to June 2022). In addition to receiving standardized  
165 treatment, the intervention group also received a multidimensional digital cardiac  
166 rehabilitation intervention, which encompassed seven dimensions: exercise training,  
167 medication management, nutritional guidance, psychological support, sleep  
168 management, health education, and smoking cessation support. It is important to note  
169 that, in addition to the intervention for patients themselves, the digital cardiac  
170 rehabilitation intervention particularly emphasized the involvement of the patients'  
171 family members. During the hospitalization period, family members were invited to  
172 participate in the rehabilitation training program, ensuring that they could provide

necessary support for the patients and promote health education within the home environment. The control group, on the other hand, received only standardized treatment and standard nursing care.

After the PCI procedure, both groups of patients underwent a three-month follow-up period. The follow-up included individualized educational sessions conducted monthly via the WeChat platform, in addition to outpatient visits at one and three months post-surgery. During the follow-up, patients were required to report their health status to the multidisciplinary intervention team, including blood pressure, physical activity, dietary habits, sleep patterns, psychological state, and progress in smoking cessation.

Only patients who completed all data collection requirements were included in the final analysis. The final dataset was subjected to propensity score matching to balance the baseline characteristics between the two groups, ensuring comparability.

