### **Study Population**

This emulated target trial was conducted at the First Affiliated Hospital of Bengbu Medical University, including 164 UA patients who underwent PCI in the Department of Cardiology from April to May 2022 (the control group) and May to June 2022 (the intervention group). Main inclusion criteria were as follows: (1) Patients diagnosed with UA who successfully underwent PCI; (2) patients classified as having cardiac function grades 1 to 3; (3) patients with no new or recurrent chest pain for at least eight hours after reperfusion therapy, no new arrhythmias or ECG changes within this timeframe, and no further elevation in myocardial injury marker levels; (4) patients capable of using a smartphone; and (5) patients who understood the purpose of this study and voluntarily provided written informed consent. The exclusion criteria were as follows: (1) patients with significant postoperative wound bleeding, severe infection, fever, severe electrolyte–acid–base imbalance, severe

hypoxia, or malnutrition; and (2) patients who were unwilling to participate in this study or unable to adhere to the follow-up visit requirements.

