***Inclusion and exclusion criteria.***

---

Inclusion criteria

---

Age between 18 and 74 years old

Patients diagnosed with UA who successfully underwent PCI

Patients classified as having cardiac function grades 1 to 3

Patients with no new or recurrent chest pain for at least eight hours after reperfusion therapy, no new arrhythmias or ECG changes within this timeframe, and no further elevation in myocardial injury marker levels

Patients capable of using a smartphone

Patients who understood the purpose of this study and voluntarily provided written informed consent

---

Exclusion criteria

---

Previous PCI surgery

Out of age

Patients with significant postoperative wound bleeding, severe infection, fever, severe electrolyte–acid–base imbalance, severe hypoxia, or malnutrition

Patients classified as having cardiac function grades 4

Patients with hepatic and renal failure

Patients with severe physical mobility impairments

Refusal to sign consent form

Mental abnormality

Not suitable for participation

---

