## Study Procedures

### Intervention Strategy

According to the UA treatment guidelines, standardized treatment is provided to all patients, alongside essential knowledge regarding UA and PCI. In the multidimensional digital cardiac rehabilitation intervention group, patients received rehabilitation therapy managed by a multidisciplinary intervention team led by nurses. In this intervention teams, the Cardiovascular Medicine Nurse Manager was the primary person responsible for management of the project. One nursing evidence-based specialist screened expert panellists; four cardiovascular clinicians

and two rehabilitation physicians were involved in the design and implementation of the program; and 2 postgraduate students, consisting of stakeholders on a multidisciplinary team, were involved in the collection of statistical data and analysis of the data.

The multidimensional digital cardiac rehabilitation intervention was delivered through a customized digital cardiac rehabilitation program. The program includes seven key dimensions of rehabilitation: exercise, medication management, nutritional guidance, psychological support, sleep management, health education, and smoking cessation assistance.

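### The covariates named for propensity matching are mainly sociodemographic and do not include cardiac function grade, or smoking status, so a systematic severity or prognosis difference between the two admission cohorts is not directly controlled.

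*Combined protocol and SAP*

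**What the plan says.** In the combined protocol and SAP, Study Design allocates patients by admission date: control in April to May 2022, intervention in May to June 2022. The Randomization section confirms that assignment was not random and relies on a logistic propensity score with 1:1 nearest-neighbour matching and a calliper of 0.2. It describes this as "considering covariates such as age, sex, education level, marital status, exercise habits, monthly salary, current address, living arrangement", and the list goes on to "history of CHD, history of PCI, length of hospitalization, medical insurance status and polypharmacy data obtained from presurveys".

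Study Population admits "patients classified as having cardiac function grades 1 to 3". The table of inclusion and exclusion criteria excludes "Patients classified as having cardiac function grades 4" and also excludes previous PCI. Eligibility further requires freedom from recent chest pain, "no new arrhythmias or ECG changes within this timeframe, and no further elevation in myocardial injury marker levels".

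Smoking is a target of the programme. Intervention Strategy counts among its dimensions "psychological support, sleep management, health education, and smoking cessation assistance", and Study Design has patients in follow-up report "psychological state, and progress in smoking cessation".

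Statistical Method gives t, Wilcoxon, chi-square or Fisher tests and no adjusted outcome model. Results reports 164 patients (89 and 75) matched to 68 per group, with non-significant baseline differences after matching. It does not say which variables were checked.

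**The concern.** When arms are consecutive admission cohorts, matching has to balance prognosis. Cardiac function grade plausibly bears on walking distance, the frailty items and physical quality of life, which are the primary outcomes. Patients in grades 1 to 3 all enter, so the cohorts can differ in their mix.

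Such a difference need not be pure chance. Screening took account of clinical stability and ability to cooperate with rehabilitation, and the two recruitment windows both include May. Only patients with complete data were analysed, so severity-related dropout could differ between an exercise programme and usual care. These are possible routes to a systematic difference; the documents do not show that any of them operated. If one did, the difference would pass into every primary comparison to the extent that the named covariates do not capture it, because no later step in the analysis adjusts for it.

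**Working it through.** **1. Content of the covariate list (Randomization section).**

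| Type | Covariates | Count |
|---|---|---|
| Sociodemographic | age, sex, education, marital status, salary, address, living arrangement, insurance | 8 |
| Lifestyle | exercise habits | 1 |
| Clinical | history of CHD, history of PCI, length of hospitalization, polypharmacy | 4 |

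Total 8 + 1 + 4 = 13, so 8/13 = 62% are sociodemographic and 4/13 = 31% clinical. If the exclusion of previous PCI was applied, history of PCI does not vary. That leaves 12 informative covariates, of which 8/12 = 67% are sociodemographic and 3 are clinical. None of those three grades current cardiac function.

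**2. Is grade available?** Grades 1 to 3 enter and grade 4 does not, so grade must be assessed for every patient. The documents imply, but do not state, that it was stored as a data item.

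**3. Is smoking status available?** Follow-up reporting of cessation progress covers both groups, but the cessation support itself is described for the intervention group. No section says that smoking status at admission was recorded in controls.

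**4. Does the reported balance check settle the matter?** The matched counts agree: 89 + 75 = 164 and 2 × 68 = 136. At 68 per group the standard error of a standardised difference is √(2/68) = 0.1715. A difference of up to 1.96 × 0.1715 = 0.34 SD therefore stays non-significant. For a binary factor, 14/68 against 24/68 (21% against 35%) gives P = 0.056 by the uncorrected chi-square test and would pass. Non-significance is weak evidence of balance even for a variable that was checked.

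**5. Illustrative size.** The plan has no figure to reproduce, and the documents give no distribution of grade or smoking. All inputs here are assumptions.

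- Bias = difference in the share of grade 3 × effect of grade 3 in SD.
- Low end: 0.05 × 0.5 = 0.025 SD.
- High end: 0.20 × 1.0 = 0.20 SD.

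For an imbalance that is fixed and systematic, the two-sided rejection rate under no treatment effect is P(|Z + bias/0.1715| > 1.96). That is 5.2% at 0.025 SD and 21.5% at 0.20 SD. A milder set of assumptions (5 to 15 points, 0.25 to 0.8 SD) gives a bias of 0.01 to 0.12 SD and 5.1% to 10.8%.

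**6. Chance imbalance is a different matter.** If 30% are grade 3 (assumed), the SD of a chance difference is √(2 × 0.3 × 0.7/68) = 0.079, about 8 points. The extra outcome variance due to grade is already in the t-test's standard error. A simulation with 68 per arm, 30% grade 3, no treatment effect and a grade effect of 0.5 or 1.0 SD rejected in 4.98% and 4.92% of 40,000 runs each. A 20-point gap arises by chance in only about 1.1% of such samples.

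**The case against.** The strongest reply is that admission date selects on severity no more than on social factors. The cohorts come from one department in adjacent periods under the same criteria, and several named covariates (age, exercise habits, CHD history, polypharmacy, length of stay) may carry part of the information in grade. This stands as a limit on the likely size: matching may partly balance grade. It does not replace balancing grade itself, which is a direct measure already needed for eligibility.

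A reader might infer four stronger things that the documents do not support.

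- **That grade was left out of the fitted model.** The list opens with an open-ended phrase and no baseline table is given. What can be said is that grade is not named.
- **That grade is the only disease measure at screening.** Chest pain, ECG or arrhythmia and injury markers are also checked, though as pass/fail stability conditions. Grade is the only ordered severity scale.
- **That type I error is inflated to as much as 21.5%.** That figure needs a systematic 20-point gap together with a 1.0 SD effect, and nothing in the documents shows either.
- **That smoking status is ready to use.** Its collection at admission in controls is not documented. Smoking is also a prognostic factor and an intervention target, not a measure of cardiac severity.

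Admission fitness measures and lipids might also stand in for functional severity, but they are not named as covariates either.

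**Conclusion.** The point holds in limited form and should be corrected. As described, the plan names no graded measure of cardiac severity and no smoking status among the covariates, and it has no outcome adjustment to make up for this. A systematic severity or prognosis difference between the cohorts is therefore not directly controlled, and the statement in Study Design that matching ensures comparability cannot be relied on for these variables. Whether such a difference exists, and how large it is, cannot be determined from the documents; the 0.025 to 0.20 SD range is an illustration under assumed inputs. The conclusion rests on the covariate list being substantially what is printed. If grade was in the model, one sentence saying so, with its standardised difference, would resolve that part.

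**What to change.** Add cardiac function grade (three levels) to the propensity model, or adjust for it in the outcome model. Do the same for smoking status at admission if it was recorded in both groups; if it was not, say so as a limitation. If the propensity model changes, re-derive the matched sample. Report standardised differences for these variables rather than relying on P values. Print the covariate list as complete, without open-ended wording, and drop history of PCI if it is constant.

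The cost is a re-run, provided grade was stored as data. Grade adds two parameters and a binary smoking variable adds one. A few matched pairs may be lost; at present 75 − 68 = 7 controls and 89 − 68 = 21 intervention patients are unmatched. The documents do not allow the loss to be predicted. Adjusting in the outcome model avoids any loss of pairs.
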